### 2.9. Statistical Analysis

#### 2.9.1. Clinical Data Analysis

All statistical analyses will be performed by a statistician from the Clinical Evaluation and Analysis Centre of Dongzhimen Hospital affiliated to BUCM using Statistical Package for the Social Sciences (SPSS) V.22.0. The statistician will be blinded to the allocation of groups. The level of significance is established at *α* < 0.05 with a two-tailed test. The main objective is to compare the change in the AQ score at week 12 from baseline between the acupoint group and the NA control group. The null hypothesis is that the acupoint group will show the same change as the NA control group, while the alternative hypothesis is that the acupoint group shows a greater improvement. Categorical data will be represented by percentages, whereas continuous data will be represented by the average, standard deviation, median, minimum value, and maximum value. For comparison with the baseline, a *t*-test or nonparametric test will be used for continuous data and nonparametric tests for categorical data. For comparison of two independent samples, if the residuals are normally distributed, the analysis of covariance (ANCOVA) will be used for the primary outcome and subgroup analysis stratified by aphasia severity, *t*-tests for other continuous data, and chi-square tests for categorical data; if the residuals are non-normally distributed, a nonparametric test will be used for both the continuous and categorical data. The results of the intention-to-treat (ITT) analysis will be used to assess the validity of the study as a whole. The ITT analysis will collect data from all the participants in this trial, and for those lost to follow-up, the last observation carried forward method will be implemented.

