## 3. Discussion

PSA has proven to be difficult to treat. There is a degree of spontaneous recovery in the subacute phase, so there are few studies on the subacute phase of PSA. However, the subacute phase also requires treatment. The extant literature shows that acupuncture is probably effective for PSA [18, 45–47]. We intend to evaluate the long-term efficacy of acupuncture in maintaining speech production function. One common problem is the lack of standardization of acupoint selection, needle retention time, number of needles used, needling depth, and needle manipulation in acupuncture research.

From 2006 to now, we attempted to explore the general acupuncture scheme based on syndrome differentiation. In our PSA acupuncture treatment programme, DU20 is located in the area at the top of the head and is particularly closely related to the regulation of brain speech activity. The EX-HN1 are the acupuncture points around the DU20, both of which are used together to benefit the brain and promote speech rehabilitation. The treatment of PSA by EX-HN12 and EX-HN13 bloodletting has a theoretical basis in TCM and unique clinical efficacy. CV23 is mainly used for the treatment of speechlessness, stabbing into the skin towards the root of the tongue, and has the effect of restoring speech. The acupuncture theory of HT5 and GB39 to be used in our study is different from the traditional meaning of these points. FMRI can help us evaluate the changes of needle-related neuroplasticity, so we have conducted fMRI experiments based on this pair of effective points for aphasia. Electroacupuncture at HT5 and GB39 may modulate language and cognition function through a complex network formed by an extensive area of the brain cortex. It is beneficial to the recovery of language function [47]. In previous studies, we have demonstrated that this acupuncture protocol has shown significant improvements in auditory comprehension, reading, and dictation in patients with subacute PSA after 4 weeks of treatment. Therefore, we would like to know more about whether this treatment programme has long-term effects in these areas and observe the association with overall linguistic changes.

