Regarding the study design, we developed an assessor- and participant-blinded design to minimize bias. The specific effects are thought to be generated by needling the acupoint with the appropriate manipulation. The nonspecific effects are due to other aspects of the therapy, such as the expectations of the patient, which might influence the treatment outcome. To recognize the specific effects, a placebo is needed. Among acupuncture research, placebo controls for acupuncture studies have been difficult to select. To maximally exclude the placebo effect, rigorous methodological designs are followed. In our study, control conditions involve being punctured with real acupuncture needles at NA locations. Thus, the self-perception of placebo effects in the NA control group is difficult to distinguish from the real acupoints. Additional needle manipulations will not be used in the NA control group. De qi is a characteristic constellation of sensations felt by patients during acupuncture needling. It has been regarded as an important factor related to clinical effects; however, we do not pursue this kind of sensation in the NA control group. By following these methods, participants can be successfully blinded, and the efficacy of acupuncture could be confirmed if the results of the acupoint group prove superior to those of the NA control group.

We will assess patients with PSA on multiple levels, including multiple neuropsychological tests, functional and structural brain alterations, and TCM syndrome evaluation. This multidomain assessment will be used to identify possible biomarkers involved in the effects of acupuncture in PSA.

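### Section 2.9.1 adds significance tests against baseline without limiting them to description, and gives unadjusted t-tests to continuous outcomes other than the primary (minor; primary analysis unaffected)

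*Protocol article*

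**What the plan says.** All the analysis rules at issue are in section 2.9.1 of the protocol article.

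- **Objective:** "The main objective is to compare the change in the AQ score at week 12 from baseline between the acupoint group and the NA control".
- **Null hypothesis:** "The null hypothesis is that the acupoint group will show the same change as the NA control group".
- **Level:** "The level of significance is established at *α* < 0.05 with a two-tailed test". It is set for the analyses in general.
- **Tests against baseline:** "For comparison with the baseline, a *t*-test or nonparametric test will be used for continuous data and nonparametric tests for categorical data". The next sentence deals separately with two independent samples, so the natural reading is a pre-post test within each arm. The article neither calls these tests descriptive nor says what may be concluded from them.
- **Between-arm tests:** if residuals are normal, "the analysis of covariance (ANCOVA) will be used for the primary outcome and subgroup analysis stratified by aphasia severity". Other continuous data get t-tests with no mention of baseline adjustment. If residuals are not normal, a nonparametric test is used.

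Elsewhere, section 3 says of these patients: "There is a degree of spontaneous recovery in the subacute phase". Section 2.5.3 gives every participant the same 12 sessions of speech and language therapy. Section 3 also says of earlier work that "this acupuncture protocol has shown significant improvements in auditory comprehension, reading, and dictation in patients with subacute PSA after 4 weeks of treatment", and names no comparator. On how efficacy would be concluded, section 3 says that "the efficacy of acupuncture could be confirmed if the results of the acupoint group prove superior to those of the NA control group".

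**The concern.** A pre-post test within one arm has zero mean change as its null. That is not the null the article states, which is equal change in the two arms. Patients enter 1 to 6 months after stroke, the article accepts that some recover spontaneously, and both arms receive speech therapy. Improvement from baseline is therefore to be expected in both arms even if acupoint needling adds nothing over nonacupoint needling.

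At stake is interpretation. A significant improvement from baseline in the acupoint arm at week 4, 12 or 24 could be read as sustained benefit. So could a significant result in that arm beside a nonsignificant one in the control arm. The risk is greatest for AQ at weeks 4 and 24 and for the secondary scales, where the article gives no explicit rule for what the p-values against baseline are for.

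A second, smaller matter concerns the same outcomes. Their between-arm comparison is assigned an unadjusted t-test, although baseline values are collected (Table 1) and ANCOVA is already planned for the primary outcome.

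**Working it through.** **Inputs from the article.** 20 analysable patients per arm, 20% drop-out, 24 recruited per arm (section 2.6); 1:1 allocation (section 2.2); two-sided 0.05 (section 2.9.1). The article gives no mean AQ change, SD or power. The shared recovery d = mean change / SD of change is therefore an assumption, shown over a range.

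**The article's own figure.** 20 × (1 + 0.20) = 24 per arm, 48 in total, which reproduces the target. Results are given for 20 per arm and also for 24, because the intention-to-treat analysis with last observation carried forward keeps all randomised patients.

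**Step 1: within-arm test, equal change in both arms.** The paired t statistic is noncentral t with n − 1 degrees of freedom and noncentrality d√n. For n = 20 the noncentrality is 0.3 × 4.472 = 1.34, 0.5 × 4.472 = 2.24 and 0.8 × 4.472 = 3.58. The chance of significant improvement in one arm is u.

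**Step 2: acupoint significant, control not.** The arms are independent with the same u, and the opposite tail is negligible for d of 0.3 or more, so the chance is about u(1 − u). At n = 20: 0.246 × 0.754 ≈ 0.19; 0.564 × 0.436 ≈ 0.246; 0.924 × 0.076 ≈ 0.070.

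| Assumed d | u, n = 20 | Acupoint only, n = 20 | u, n = 24 | Acupoint only, n = 24 |
|---|---|---|---|---|
| 0.2 | 13% | 12% | 15% | 13% |
| 0.3 | 25% | 19% | 29% | 21% |
| 0.5 | 56% | 25% | 65% | 23% |
| 0.8 | 92% | 7% | 96% | 4% |
| 1.0 | 99% | 1% | 99.7% | 0.3% |

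The control arm has the same u in every row. u passes 50% at d of about 0.46 (n = 20) or 0.42 (n = 24).

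**Step 3: the planned between-arm test under the same conditions.** A baseline-adjusted ANCOVA was simulated with 20,000 replicates per setting, 20 per arm, d of 0.5, 0.8 and 1.0, and an assumed baseline to week-12 correlation of 0.5 or 0.8. It was significant in 4.7% to 5.1% of trials, and in favour of acupoint in 2.3% to 2.6%, whatever the shared recovery.

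**Step 4: what adjustment gains for the other continuous outcomes.** With equal variances (set to 1) at baseline and follow-up and correlation r, the per-patient variance is 1 for the follow-up score, 2(1 − r) for the change score and 1 − r² for ANCOVA.

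- r = 0.5: 1, 1.00 and 0.75.
- r = 0.8: 1, 0.40 and 0.36.

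ANCOVA therefore has 75% or 90% of the variance of a t-test on change, and 75% or 36% of that of a t-test on the follow-up score. It costs one degree of freedom (37 instead of 38 at 20 per arm). The correlations are assumed.

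**The case against.** **The stated null is tested.** A reader might infer that the tests against baseline stand in for the test of equal change. The article does not support that. The sentence after them assigns ANCOVA to the primary outcome and between-arm tests to the rest, and the discussion ties efficacy to superiority over the control group. No section bases an efficacy conclusion on a within-arm test. This objection stands in full for the primary outcome.

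**No error rate is inflated.** A reader might set 56% or 92% beside 5% and speak of an inflated false-positive rate. If patients recover, rejecting no change is correct; those figures are power against a false null. What would be wrong is to carry the result over to acupuncture.

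**The size is assumed and the two risks do not peak together.** It also overstates the matter to say the acupoint arm will usually look improved, since that needs d of about 0.46 or more at 20 per arm. When d is large, the control arm is nearly always significant too and the shared recovery is plain to see. Counting every trial in which exactly one arm is significant gives 49% at d = 0.5, but half of these favour the control arm.

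**The remark about earlier studies proves little.** It does not say whether those improvements were within or between arms. The introduction reports an earlier acupuncture-versus-control comparison with a nonsignificant week-4 difference. A habit of within-arm inference cannot be established from this.

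**An article condenses.** The full protocol or SAP may label these tests descriptive. That is fair, and it lowers the severity. But the article does state the baseline tests, at a common significance level, and does state t-tests for the other continuous outcomes. The discussion sentence on superiority is not an analysis rule for weeks 4 and 24 or for the secondary scales.

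**Conclusion.** The point holds as a minor one. Section 2.9.1 adds tests against baseline that cannot bear on the effect of acupoint needling, and does not confine them to description. In this setting they can readily be significant when the arms change equally: about 25%, 56% or 92% for the acupoint arm's own test at d of 0.3, 0.5 or 0.8 with 20 per arm. The misleading split, acupoint significant and control not, arises in about 19%, 25% or 7%, against about 2.5% for a between-arm false positive favouring acupoint.

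These figures rest on approximately normal change scores, independent arms, equal mean change and SD in both arms, and an assumed d for which the article gives no value. The reading of the tests as within-arm is the likeliest one but is not spelled out.

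The primary analysis, its 5% level and the between-arm efficacy criterion are not called into question. Separately, the unadjusted t-tests for other continuous outcomes forgo precision that the baseline data already collected would provide.

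**What to change.** In section 2.9.1:

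1. Replace the tests against baseline with within-arm change reported descriptively, as a mean with 95% CI for continuous scores.
2. State that every efficacy or long-term-efficacy statement, including AQ at weeks 4 and 24 and the secondary scales, rests on the between-arm difference at that visit adjusted for the baseline value of the same measure. Where a score is treated as continuous, use ANCOVA in place of the unadjusted t-test.

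The primary analysis stays as it is. The change needs a few sentences and no extra patients, visits or data. The cost is the loss of the within-arm p-values, and one degree of freedom in each adjusted comparison. If the full protocol or SAP already says this, aligning the published text is enough.

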### 2.2. Randomization and Blinding

Eligible patients will be randomly assigned to the acupoint group or NA control group with a 1 : 1 ratio. The randomization sequence will be generated by a third-party professional statistician using a computer-generated randomization digital table using SAS V.9.4 software (SAS Institute Inc., North Carolina, USA). An independent assessor will interview the participants and carry out the screening. Random numbers and group assignments will be confirmed immediately through short message service to the practitioners who conduct acupuncture. All participants will be blinded to the types of acupuncture. An independent, blinded assessor who does not know the group assignment will conduct the outcome evaluation after the treatment. The researcher who will oversee the statistical analysis will also be blinded, with the treatment for each group remaining unknown; however, it is impossible to blind practitioners who conduct acupuncture. The practitioner will be forbidden from discussing the type of acupuncture with the participants. We will endeavour to ensure that subjects begin the trial with similar expectations of efficacy by informing them that the provided treatments are effective. In this study, participants, assessors, and statisticians will be blinded to treatment allocation. Participants will receive treatments alone at different times to avoid communication with each other. An eye patch will be applied to patients during the acupuncture treatment. To minimize the unintentional physical cues and bias in this trial, acupuncturists will be required to emulate the same procedure for the nonacupoint control group. In addition, participants will be asked to answer the following question during week 4 to test the blinding effect: “Do you think you have received real acupuncture treatment?” The participants can choose “yes” or “no” as an answer [37, 38]. The percentage of participants who answered “yes” in both groups after the final treatment will be analyzed. If the results show no significant difference in the response to this question between the two groups, they could suggest that the blinding effect is sufficient.

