### 2.6. Sample Size Calculation

No large RCTs have been carried out within the field examining the long-term effects of acupuncture on PSA. Previous studies have used interventions not applicable to the current protocol and have been of varying quality and used small sample sizes. We were, therefore, unable to calculate the prior accurate sample size. Thus, our RCT will support a more accurate sample size estimate and inform a definitive trial examining the long-term effectiveness of acupuncture for aphasia. The study involves the experimental study of functional magnetic resonance imaging (fMRI) and EEG for language tasks, which falls under the scope of experimental psychology. Taking into account individual psychological differences, it is expected that the PSA patients to be included will be divided into 2 groups. The number of patients to be included in the statistics in each group will be 20. Considering a drop-out rate of 20%, the target recruitment number is 48 participants (24 per group).

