#### 2.9.2. MRI Data Analysis

For imaging, data will be analyzed using the Data Processing & Analysis for (Resting-State) Brain Imaging (DPABI) toolbox [44] performed on MATLAB V.8.6 (MathWorks) to detect any changes in brain function due to acupuncture treatment. Lesion symptom mapping was demarcated on T1-weighted images manually using MRIcroGL (http://www.cabiatl.com/mricrogl/) in native space by neurologists who were blinded to the participants' language scores. DTI images will be analyzed using MATLAB (https://www.mathworks.com/) and FMRIB Software Library (http://www.fmrib.ox.ac.uk/fsl). After data preprocessing, some data-driven approaches will be performed to investigate neuroplasticity between the two groups, such as the amplitude of the low-frequency fluctuation, regional homogeneity, and voxel-wise degree centrality. A two-sample *t*-test will be conducted to investigate the differences in brain regions between the acupoint group or NA control group in the DPABI software. Multiple comparisons will be used to better control for a highly inflated false positivity rate. Pearson's correlation analysis will be performed to examine the association between the fMRI data and clinical variables.

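### Primary ANCOVA hinges on a residual-normality check with an unnamed fallback, and clinical secondary and MRI outcomes are compared by t-tests with no baseline covariate

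*Protocol article*

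**What the plan says.** Section 2.9.1 sets the main objective as a between-arm comparison of AQ change from baseline to week 12, at a significance level of "< 0.05 with a two-tailed test". When residuals are normal, ANCOVA is used for the primary outcome and for a subgroup analysis by aphasia severity, and t "tests for other continuous data, and chi-square tests for categorical data". The ANCOVA covariates are not named. The section then adds: "if the residuals are non-normally distributed, a nonparametric test will be used for both the continuous and categorical data". That clause has no exception for the primary outcome, and it names neither the check nor the replacement test.

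Section 2.9.2 says that a two-sample t "test will be conducted to investigate the differences in brain regions between the acupoint group or NA control group", with no covariate stated.

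Baseline values exist for these measures. The Abstract puts assessments at baseline and weeks 4, 12 and 24, section 2.7.1 repeats this for MRI, and Table 1 lists a first assessment and three later ones for the Western Aphasia Battery, the Boston examination, the prognosis scale and MRI.

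On size, section 2.6 says: "The number of patients to be included in the statistics in each group will be 20". It gives no power, effect size or standard deviation: "We were, therefore, unable to calculate the prior accurate sample size".

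**The concern.** There are two linked weaknesses.

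First, the primary test is chosen after looking at the residuals. Two analysts could judge the same residuals differently, or choose different nonparametric tests, and report different primary results from one data set. An ordinary rank test also gives no baseline-adjusted estimate of the mean change, which is what the objective asks for. Section 2.6 wants this trial to inform the size of a definitive one, and an adjusted mean difference with its residual SD is the natural input for that.

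Second, the clinical secondary outcomes and the MRI measures are compared without a baseline covariate. With about 20 per arm and no stratification described in section 2.2, chance differences in baseline severity are to be expected. A t-test on follow-up values carries them into the result, and a t-test on change over-corrects for them unless the correlation is 1. Either way, precision is lost that the data already collected could supply.

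**Working it through.** **Inputs from the article.** Two-sided alpha 0.05 (2.9.1); 1:1 allocation (2.2); 20 analysed per arm, 20% dropout, 48 recruited (2.6).

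**Assumptions.** The correlation r between baseline and follow-up is not in the article, so a range is shown. The SD is taken as equal at both times and set to 1. Effects of 0.5 and 0.65 SD are illustrative.

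**The plan's own figure.** 20 × 1.2 = 24 per arm, or 48 in all, which reproduces. Dividing by the retained fraction gives 20 / 0.8 = 25 per arm, or 50. With 24 recruited, 24 × 0.8 = 19.2 remain, so about 20 per arm is a fair basis. There is no power figure to reproduce.

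**Precision.** Outcome variances are 1 for follow-up, 2(1 − r) for change and 1 − r² for ANCOVA. ANCOVA relative to change is therefore (1 − r²) / [2(1 − r)] = (1 + r)/2, and relative to follow-up it is 1 − r². The t-test sample size that matches ANCOVA with 20 per arm is 20 divided by that ratio.

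| r | Change variance | ANCOVA variance | Reduction vs change | Matching n, change | Reduction vs follow-up | Matching n, follow-up |
|---|---|---|---|---|---|---|
| 0.3 | 1.40 | 0.91 | 35% | 30.8 | 9% | 22.0 |
| 0.5 | 1.00 | 0.75 | 25% | 26.7 | 25% | 26.7 |
| 0.7 | 0.60 | 0.51 | 15% | 23.5 | 49% | 39.2 |
| 0.8 | 0.40 | 0.36 | 10% | 22.2 | 64% | 55.6 |
| 0.9 | 0.20 | 0.19 | 5% | 21.1 | 81% | 105.3 |

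The ratios do not depend on the sample size.

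**Detectable difference at 80% power.** This is SD × √(2/20) × (1.960 + 0.842) = 0.886 × SD. At r = 0.7 it is 0.886 × √0.60 = 0.69 for change, 0.886 × √0.51 = 0.63 for ANCOVA, and 0.89 for follow-up.

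**Power at r = 0.7.** For a true effect of 0.65 SD (noncentral t, 20 per arm): ANCOVA 80%, t-test on change 73%, t-test on follow-up 52%.

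**The switch.** Simulated trials of 20 per arm (3,000 per setting) compared ANCOVA with the Mann-Whitney test on change. Skewed errors were standardised lognormal with log-SD 0.8.

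| r | Errors | ANCOVA type I error | Power at 0.5 SD, ANCOVA | Power at 0.5 SD, Mann-Whitney on change |
|---|---|---|---|---|
| 0.5 | normal | 4.9% | 41% | 32% |
| 0.5 | skewed | 4.3% | 53% | 49% |
| 0.8 | normal | 4.6% | 72% | 66% |
| 0.8 | skewed | 4.4% | 77% | 92% |

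ANCOVA kept its type I error under skew, so non-normal residuals did not by themselves require dropping it. Neither test dominates on power. In a further simulation at r = 0.7 and 0.65 SD, the two tests disagreed on significance in about 14% of trials, so the choice between them can decide the reported conclusion.

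Simulating the whole procedure with a Shapiro-Wilk check (2,500 trials, 0.5 SD, gamma errors with shape 2) gave power of 41% against 45% for fixed ANCOVA at r = 0.5, and 77% against 72% at r = 0.8. Across settings its type I error was 4.4% to 6.3%.

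**The case against.** The strongest defence is that a t-test between randomised arms is valid, so baseline adjustment buys efficiency rather than validity. The imaging work is partly exploratory, and a condensed article may leave the covariates and the name of the fallback test to an analysis plan. That stands in part. Missing detail alone would be no finding, and the secondary and MRI part concerns precision only. But the conditional rule for the primary outcome and the choice of t-tests are stated in the article.

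A reader might infer four stronger claims that the article does not support:

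- **That every continuous outcome other than the AQ gets a t-test.** Sections 2.9.3 and 2.9.4 state no between-arm test for EEG or ERP, the t-test rule sits under the clinical analysis, and the severity subgroup also gets ANCOVA.
- **That baseline data are discarded.** The primary outcome is a change from baseline, so a rank test on it still uses baseline. For the other outcomes the text does not say whether change or follow-up values are tested.
- **That the loss is 25% to 64% of variance.** Those figures hold only for t-tests on raw follow-up values.
- **That the nonparametric switch costs power.** Under strong skew it can gain, as the 92% against 77% result shows.

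The ANCOVA covariate is also unnamed. Baseline AQ is the natural reading, but it is a reading.

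**Conclusion.** The concern holds in limited form. The primary test should not depend on a residual check with an unnamed fallback: the selection is data-dependent, and the adjusted estimate of mean change can disappear. This does not rest on any assumed correlation.

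For the continuous clinical secondary outcomes and MRI measures, unadjusted t-tests give up precision. On change scores the gain from ANCOVA is modest: 10% to 25% of variance for r of 0.5 to 0.8, so 20 per arm works like 22 to 27. It is larger only if follow-up values are tested. These sizes rest on the assumed correlation and equal SDs, and the power figures also on illustrative effects. In theory ANCOVA is at least as efficient on either reading, so the recommendation does not depend on which was meant. The change should be made, but the point does not invalidate the trial.

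**What to change.** 1. **Primary.** Specify ANCOVA of week-12 AQ, or of its change, with baseline AQ as covariate, whatever the residuals show. Both versions give the same treatment estimate. A robust standard error or a permutation p-value can be added if non-normality is a worry.
2. **Switch.** Delete the residual-normality rule. Report a rank-based, baseline-adjusted analysis as a named sensitivity analysis only.
3. **Continuous clinical secondary outcomes and MRI measures.** Replace the plain t-tests with between-arm models that carry the baseline value of the same measure as covariate.

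The cost is wording, settled before the data are unblinded. No extra visits, measurements or patients are needed.

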**Methods:**

This is a multicentre, randomized, blinded, nonacupoint (NA) acupuncture controlled, multimodal neuroimaging clinical trial. A total of 48 subjects with subacute PSA will be randomly assigned to an acupoint group or an NA control group. The acupoint group will receive acupuncture with normal needling at DU20, EX-HN1, HT5, GB39, EX-HN12, EX-HN13, and CV23. The NA control group will receive acupuncture in locations not corresponding to acupuncture points as sham acupoints. Both groups will receive identical speech and language therapy thrice a week for four weeks. The primary outcome will be the change in the aphasia quotient (AQ) score measured by the Western Aphasia Battery (WAB) test during the 12th week after randomization. Participants will be blindly assessed at prerandomization (baseline) and 4 weeks, 12 weeks, and 24 weeks after randomization. The secondary outcomes include the Boston Diagnostic Aphasia Examination (BDAE) score, the Disease Prognosis Scale score for ischaemic stroke, etc. Magnetic resonance imaging (MRI) and electroencephalogram (EEG) will also be performed at 4-time intervals as secondary outcomes. All scores and image evaluations will be taken at the same point as the linguistic evaluation. The multilevel evaluation technique will be used to assess the long-term efficacy of acupuncture therapy. MRI scans and EEG will be used to assess acupuncture-related neuroplasticity changes. *Discussion*. The results from our trial will help to supply evidence for the long-term acupuncture effects for PSA over a long follow-up period. It will provide valuable information for future studies in the field of PSA treatment. The trial was registered at the Chinese Clinical Trial Registry on 16 March 2020 (ChiCTR2000030879).

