### 2.4. Eligibility Criteria

#### 2.4.1. Inclusion Criteria

Participants meeting all of the following criteria will be included in this trial: (1) diagnosed as stroke through computed tomography (CT) or MRI, 1 to 6 months after stroke onset; (2) 30 to 80 years of age (After the expert discussion and the actual situation of our country, the age range has been adjusted), the native language is Chinese, and right-handed; (3) primary school and above education with no serious heart, liver, or kidney diseases; (4) clear consciousness and no cognitive impairment; (5) normal language function before the stroke onset and dominant language dysfunction with mild limb dysfunction; (6) specific aphasia syndrome diagnosed as motor aphasia by the WAB; (7) BDAE score of 2 to 4; and (8) able to cooperate for the 30-minute MRI examination.

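### The test for categorical outcomes hinges on normal residuals, a condition that does not apply to them, and the BDAE is left with no classified scale and no stated baseline adjustment

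*Protocol article*

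**What the plan says.** Section 2.9.1 sets one switch for comparing the two groups. If residuals are normal, it uses ANCOVA for the primary outcome and for a subgroup analysis by aphasia severity, t-tests for other continuous data, and "chi-square tests for categorical data". Otherwise, "if the residuals are non-normally distributed, a nonparametric test will be used for both the continuous and categorical data". The nonparametric test is not named. Significance is set at "0.05 with a two-tailed test".

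On the BDAE, the Abstract states: "The secondary outcomes include the Boston Diagnostic Aphasia Examination (BDAE) score". Section 2.4.1 requires a "BDAE score of 2 to 4" at entry, so a baseline value exists for every patient. The Abstract and Table 1 schedule a baseline assessment (shown under week 1 in Table 1) and assessments at weeks 4, 12 and 24. Nowhere is the BDAE described as continuous, ordinal or categorical.

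On size, section 2.6 says "The number of patients to be included in the statistics in each group will be 20" and "Considering a drop-out rate of 20%, the target recruitment number is 48 participants (24 per group").

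**The concern.** Two things are wrong in what the section states.

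First, the switch has no meaning for categorical data. A chi-square test on a table does not assume normal residuals, so there is nothing to check. If the residuals meant are those of the primary ANCOVA, they say nothing about how a different, categorical outcome should be tested. The choice between chi-square and an unnamed test therefore has no working rule behind it and would have to be settled once the data are in hand.

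Second, ANCOVA is the only covariate-adjusted method named, and its scope is limited to the primary outcome and the severity subgroup. A secondary such as the BDAE has no stated between-group analysis that adjusts for baseline. Because its scale type is also open, three routes are available: t-test, chi-square or nonparametric test. They differ in whether they use the order of the scores. With about 20 patients per arm, ignoring order and baseline can decide whether a real shift is seen.

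**Working it through.** **The plan's own figure.** 20 × (1 + 0.20) = 24 per group, or 48 in total, which reproduces the recruitment target. Dividing instead, 20 / (1 − 0.20) = 25 per group, or 50, differs by two patients and does not matter here. The plan states no power, effect or variance for the BDAE, so everything below rests on assumptions, shown as ranges.

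**Inputs from the protocol article.** Two-sided 5% (2.9.1); 1:1 allocation (2.2); 20 analysed per group (2.6); entry score 2 to 4 (2.4.1).

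**Measure.** Share of power lost = 1 − (power of the test) / (power of the baseline-adjusted ordered reference).

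**Model A (latent normal, 4,000 runs per cell).** Assumed: baseline grades 2–4, follow-up grades 0–5, cut points 1 SD apart, common gain 0.5 SD, treatment shift 0.5 to 1.0 SD, baseline–follow-up correlation 0 to 0.85. The reference is the baseline-stratified Wilcoxon test. Power (%) at 20 per arm and a shift of 0.8 SD:

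| Correlation | Chi-square | t-test, follow-up value | Wilcoxon, follow-up value | Wilcoxon, change | Stratified Wilcoxon | ANCOVA on score |
|---|---|---|---|---|---|---|
| 0 | 38.3 | 65.0 | 63.9 | 40.8 | 60.8 | 63.8 |
| 0.5 | 38.1 | 63.8 | 63.0 | 62.6 | 68.2 | 71.9 |
| 0.7 | 38.7 | 65.0 | 63.6 | 77.4 | 78.6 | 81.5 |
| 0.85 | 37.9 | 64.4 | 63.2 | 90.8 | 90.2 | 91.4 |

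- Chi-square loss at this shift: 1 − 38.3/60.8 = 37%; 1 − 38.1/68.2 = 44%; 1 − 38.7/78.6 = 51%; 1 − 37.9/90.2 = 58%.
- Chi-square extremes over all shifts: 1 − 58.2/78.9 = 26% (shift 1.0, correlation 0) and 1 − 16.0/53.7 = 70% (shift 0.5, correlation 0.85).
- Wilcoxon on the follow-up value, shift 0.8: no loss at correlation 0; then 1 − 63.0/68.2 = 8%, 1 − 63.6/78.6 = 19% and 1 − 63.2/90.2 = 30%. Its worst case is 1 − 31.4/53.7 = 42% (shift 0.5, correlation 0.85).
- Wilcoxon on change, shift 0.8: 1 − 62.6/68.2 = 8% at correlation 0.5 and 1 − 77.4/78.6 = 2% at 0.7. With no correlation, change is the poor choice: 1 − 40.8/60.8 = 33%.
- With no treatment effect, chi-square rejected in 3.6–4.0% of runs and the other tests in 4.6–5.6%. A little of the chi-square loss is therefore conservatism in sparse tables.
- At 24 per arm, shift 0.8, correlation 0.7: chi-square 46.3%, Wilcoxon 71.3%, stratified Wilcoxon 86.0%. Chi-square loss: 1 − 46.3/86.0 = 46%.

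**Model B (proportional odds, 600 runs per cell).** Assumed: four grades at week 12, control distribution 20/30/30/20%, baseline effect 1.5 log-odds per grade, 20 per arm. Power at a common odds ratio of 3 / 4 / 5:

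- chi-square 21 / 26 / 37%;
- Mann-Whitney on the week-12 value 31 / 43 / 55%;
- proportional odds with baseline 49 / 61 / 77%.

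Chi-square loss: 1 − 21/49 = 57%, 1 − 26/61 = 57%, 1 − 37/77 = 52%. Mann-Whitney loss: 1 − 31/49 = 37%, 1 − 43/61 = 30%, 1 − 55/77 = 29%. The t-test at odds ratio 4 had 44%: 1 − 44/61 = 28%.

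A separate run of the same model (1,500 per cell) tested change scores: t-test 43 / 57 / 68% and Mann-Whitney 44 / 57 / 70%, against 49 / 64 / 75% for proportional odds. The losses run from 1 − 70/75 = 7% to 1 − 43/49 = 12%.

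A further run at odds ratio 4, with baseline effects of 0.75 and 1.5, gave chi-square 32–38%, tests on week-12 values 50–60%, tests on change 50–61%, ANCOVA 63% and proportional odds 67%. Chi-square loss: 1 − 38/67 = 43% to 1 − 32/67 = 52%.

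**Size of the proportional-odds likelihood-ratio test at 20 per arm.** 6.5% in 600 null runs and 6.3% in 3,000. A set of 1,000 runs gave 4.6–5.2% across the tests compared.

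**The case against.** A reader might infer that the BDAE falls to chi-square by default and so loses most of its power. The article does not support that. It calls the BDAE a score, which most naturally leads to the t-test, or to a rank test if residuals are not normal, and both use the order. Loss of about half or more in the tables above is confined to the chi-square route, and even there it needs a strong baseline relation or a small effect in model A. Model B also flatters its own reference, because the data were generated from the model used to analyse them.

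The statement that no route uses baseline can also be pressed too far. The section does not say whether secondaries are compared as follow-up values or as changes; the primary is a change. A test on change uses baseline and is close to the adjusted analysis when the correlation is 0.5 or more.

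Other points reduce the stakes. Chi-square is itself usually classed as nonparametric, so the second branch may alter nothing for some items. The statistician is blinded to allocation, which limits selective choice. The BDAE is one of four secondary items (2.8.1), has no stated confirmatory role, and sits in a 48-patient trial meant to inform a larger one. Scale type and covariates for a secondary are often left to a full protocol or SAP.

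All of this stands, and it limits the size of the point. It does not rescue the rule. The article does state how the test for categorical data is chosen, and the criterion does not apply to such data. If the second branch changes nothing, the condition is empty and should go. The article also states where ANCOVA applies, and the BDAE lies outside that scope.

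**Conclusion.** The point holds in a limited form. The selection rule for categorical data is wrong as written, and the plan states no baseline-adjusted between-group analysis for a named secondary whose baseline is collected. Those two statements need no assumption.

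The size depends on the route and on assumed effects, since the documents give none for the BDAE. If chi-square were used, about 26% to 70% of the power of a baseline-adjusted ordered analysis would be lost at 20 per arm. If a t-test or rank test on the follow-up value were used, the loss would be smaller: about 30% or a little less at odds ratio 4 in model B, and in model A anything from none (baseline unrelated) to about 42% (small effect, correlation 0.85). On change scores the loss is small when baseline is well related to outcome. The primary analysis is not affected by this point.

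**What to change.** Amend section 2.9.1 in three respects:

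1. Remove the normality condition for categorical data.
2. Use chi-square, or Fisher's exact test where expected counts are small, for binary or unordered items such as the yes/no blinding answer.
3. State that the BDAE is analysed as an ordered outcome with baseline BDAE included, by one method named in advance: a baseline-stratified Wilcoxon test, ANCOVA on the score, or a proportional-odds model with baseline.

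Any of the three methods would do; proportional odds need not be imposed. It assumes a roughly common shift across grades, and its likelihood-ratio test may run slightly above 5% at 20 per arm. The cost is a few sentences of wording. No new data, visits or patients are needed.
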